## **6. Procedures for Track 1**

### 6a. Overview of study procedures

Figure 2 illustrates the main steps in the study for the prospective groups in Track 1 (non-pregnant adult population). Each step is described in detail in the following paragraphs. Track 2, which is an observational pre/post evaluation, is also described below.

Figure 2. Procedures for Track 1 (Non-Pregnant Adults)

[figure not shown]

## 6b. Screening, consent, and assignment to study group

Procedures for subjects enrolled in Track 1 are described below.

### *6b i. Identification of potential study subjects (pre-screening)*

Track 1 will recruit non-pregnant patients who, on the day of study screening:

- Have a positive HIV test at the VCT service at the study site; or
- Have blood drawn for a CD4 count; or
- Have returned to the study site for a CD4 count result and it is  $\leq 350$ .

Patients are not eligible for study screening if they have returned to the site to receive a CD4 count result on the day of study screening and the CD4 count is  $> 350$ .

At the study site, the site's staff will inform potentially eligible patients about the study immediately after routine post-test counseling, CD4 count blood draw, or return of CD4 count results. The site staff will explain that a study is underway and that patients who voluntarily enroll in the study and are found to be eligible for ART may have the opportunity to initiate treatment immediately, rather than following the standard schedule of visits. Patients who indicate that they may be interested in participating in the study will be referred to a study assistant. Those who do not wish to participate will proceed with a standard pre-ART care visit.

Site counselors who perform the pre-screening will record in a notebook (pre-screening log) patients whom they do not refer for screening, to allow the study to collect aggregate statistics about the overall patient population and compare it to the screened population. Fields that will be recorded in this notebook are date, sex, age in years, and primary reason for not being screened. (We anticipate three main reasons: patient's emotional condition; patient's physical condition; refusal. An "other" field will allow the counselor to record any other reason for not referring the patient to the study assistant for screening.) No identifiers of any kind will be collected in this notebook, which is intended to provide only aggregate information.

### *6b ii. Screening and informed consent*

Upon referral to the study assistant, patients will receive a more complete description of the study, including the details of why it is being done, the process of randomization, the steps that will occur for patients in each group, and the need for written informed consent. They will be assured that participation is voluntary and that they can withdraw from the study at any time, without affecting the quality of care provided by the site. They will also be offered the opportunity to ask questions. If the study assistant concludes that all other inclusion/exclusion criteria have been met (with the exception of treatment eligibility) they will then be asked to provide written informed consent to participate. The study assistant will complete a screening form to record study eligibility for each patient screened. The screening form will not collect any identifiable information pertaining to individual patients prior to receipt of written informed consent.

Patients will be recruited consecutively, as they arrive at the study site. Due to the volume limitations of the technology to be used in the study, however, recruitment may be staggered over the course of each day to ensure that patients randomized into the rapid initiation group can actually be offered same-day

initiation. Patients who arrive late in the day and are randomized to rapid initiation (Track 1) will be asked to return the next day, or as soon as possible, to complete all procedures.

The study information sheet and consent form will be translated into the South African languages most commonly spoken by patients at the study site. These are Isizulu, Xitsonga, and Sesotho, but additional or other languages will be included if necessary. Translated consent documents and attestation of consent accuracy will be submitted to the BUMC IRB and Wits HREC prior to use with any study subjects.

For patients who decline to participate in the study (consent refused), the study assistant will indicate the refusal on the screening form.

#### *6b iii. Questionnaire*

After a subject consents to be in the study, the study assistant will administer a short questionnaire documenting the subject's basic demographic and socioeconomic characteristics, primary reason for seeking an HIV test or HIV care, and costs incurred per clinic visit. Height and weight will be recorded to help assess balance between the two study groups (rapid and standard). As the questionnaire elicits only simple responses and will be completed by the study assistant not the subject, we do not intend to translate the questionnaire itself into subjects' first languages. Instead, for subjects who do not speak English, the assistant will ask the questions in one of the commonly-understood languages used by the study population, and then record the answers in English on the questionnaire. This approach has been used successfully in other studies in similar populations (e.g. BUMC H-24379/HREC M041116).

(Note: the questionnaire is included in the study case report form in the appendix to this protocol.)

#### *6b iv. Randomization and blood draw*

After the questionnaire has been completed, subjects will be randomized to the rapid or standard groups of the study. Randomization envelopes will be generated in blocks of 6 and kept at the study site. For each enrolled subject, the study assistant will open the next envelope in sequential order, read the randomization group, and record it on the case report form.

Depending on the randomization group, the study assistant will then ask subjects in the standard group to return to the clinic nurse for a blood draw for a standard CD4 count and subjects in the rapid group to go to the study nurse for a blood draw for a rapid CD4 count. Following the blood draw, the study assistant or study nurse will inform subjects of their group assignment. Standard group subjects will be asked to proceed with a standard pre-ART care visit. The study assistant will repeat the explanation of next steps in the study, which are limited to review of medical records by the study team, and thank them for their willingness to participate in the study. The study team will have no further personal contact with patients in the standard group.

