#### **5. Study Design**

##### 5a. Overview of study design

The study will be divided into two tracks, based on the study populations to be included.

Track 1: *Non-pregnant adults*. Track 1 will be a randomized comparison of rapid initiation of ART to the current standard of care for non-pregnant, treatment eligible adults. Patients testing positive, providing a blood sample for a CD4 count, or receiving a CD4 count result will be individually randomized 1:1 to either the rapid ART initiation strategy (rapid group) or the standard ART initiation strategy (standard group). Patients in the rapid group who are found to be eligible for ART will be offered the opportunity to initiate ART in the fastest time feasible given individual circumstances, and whenever possible on the same day as study enrollment. Patients in the standard group will be offered standard treatment initiation as currently implemented by the study site.

Track 2: *Pregnant women*. Track 2 will be a programmatic evaluation of rapid initiation of ART for pregnant women. Immediate ART initiation on the day of a woman's first antenatal care visit was introduced in South Africa in a guideline revision in April 2013 and is now the standard of care at the study site. Guidelines call for women to remain on ART for the duration of pregnancy regardless of their initial CD4 count. Adherence to ART during pregnancy, as measured by monthly medication pickups, will be compared to adherence before rapid initiation was offered.

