#### *Exclusion criteria:*

- Currently on ART or on ART at any time in the past 12 months (three-drug combination; previous PMTCT regimen exposure for an earlier pregnancy is not an exclusion criterion)
- Stated intention to seek further HIV care during the next 12 months or antenatal care before completion of the current pregnancy at another site, not at the study site
- Not physically or emotionally able to participate in the study, in the opinion of the investigators
- Not willing or able to provide written informed consent to participate in the study

- Previously enrolled in the same study
- Diagnosed with drug-resistant TB or on MDR-TB treatment
- For Track 1 only, pregnant (pregnancy is an exclusion criterion for Track 1 because treatment guidelines for pregnant women differ from those for non-pregnant adults)

*\*Current South African treatment eligibility criteria for non pregnant HIV-positive adults are:*

- *CD4 count  $\leq$  350; or*
- *Tuberculosis, regardless of CD4 count; or*
- *WHO Stage 4 or Stage 3 condition, regardless of CD count (hereafter “Stage 4/3”)*

*All pregnant HIV-positive women are eligible for ART.*

Subjects in Track 1 will be followed prospectively and will be asked for written informed consent prior to study enrollment. An additional Track 1 retrospective comparison group will be enrolled comprised of patients who became eligible for ART at one of the two study sites (Thuthukani Clinic) prior to the launch of the study, with data collection limited to retrospective medical record review. In Track 2, subjects offered rapid initiation by the study clinic under the new standard of care will be followed prospectively and asked for written informed consent before study enrollment. For subjects in the comparison group in Track 2, data will be collected retrospectively through medical record review only. The study team will have no contact with these subjects, and informed consent will not be sought.

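### With a single fixed block of 6 and on-site envelopes opened by the recruiting assistant, a quarter of Track 1 allocations can be foreseen by an assistant who knows the block size and tracks the sequence

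*Protocol*

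**What the plan says.** Protocol section 6b iv fixes the allocation method: "Randomization envelopes will be generated in blocks of 6 and kept at the study site". For each subject "the study assistant will open the next envelope in sequential order, read the randomization group, and record it" on the case report form. The assistant then directs the subject to the clinic nurse or the study nurse according to group, so the assistant knows every allocation made. Section 5a sets individual 1:1 randomization.

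The same role controls entry:

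- Section 6b ii leaves the non-ART criteria to this person: "If the study assistant concludes that all other inclusion/exclusion criteria have been met", consent is then sought.
- The same section adds: "The study assistant will complete a screening form to record study eligibility for each patient screened".
- Section 12e has a trained study assistant administer the consent form.
- Section 9 provides at most two study assistants.

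Two provisions leave room for judgement about who enters and when. Section 6b ii says "recruitment may be staggered over the course of each day", so that the rapid group can be offered same-day initiation. Section 5c excludes a patient who is "Not physically or emotionally able to participate in the study, in the opinion of the investigators".

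The protocol also contains safeguards. Recruitment is consecutive (6b ii). Site counselors make the first referral and log patients they do not refer, with the reason (6b i). Refusals go on the screening form (6b ii). The envelope is opened only after consent and the questionnaire (6b iii and 6b iv).

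**The concern.** Opening envelopes in sequence conceals the next allocation only if it cannot be worked out from earlier ones. With one block size, printed in the protocol, and past allocations known to the person who recruits, the end of each block can be worked out by counting. Envelopes that are sealed and opaque would not change this, because the inference comes from the past sequence and not from the envelope.

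The primary outcome is sensitive to who is recruited. Under section 11a i, a subject without a six-month viral load within 10 months counts as a failure, so retention weighs as much as suppression. Section 3c expects some patients to accept immediate treatment before they are ready and then to drop out. A recruiter may sense readiness in conversation. It is not among the confounders named in section 11b, so the planned regression adjustment might not correct for selection on it.

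**Working it through.** The protocol gives no figure for predictability, so there is none to reproduce. Its sample size, which this point does not depend on, does reproduce: 50% v 70%, two-sided 5% (two-sided is assumed), 90% power and no continuity correction give 124 per group.

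**Inputs.** Block size 6 (6b iv); ratio 1:1, so 3 rapid and 3 standard per block (5a); up to 600 consented and 400 enrolled (section 10). **Assumption:** the observer knows the block size and sees every allocation in the sequence.

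**Certain allocations.** There are C(6,3) = 20 equally likely orderings. An allocation is certain once the three places of one arm are used up.

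| Certain allocations at end of block | Orderings |
|---|---|
| last 1 | 12 |
| last 2 | 6 |
| last 3 | 2 |

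Mean = (12×1 + 6×2 + 2×3)/20 = 30/20 = 1.5 per block, and 1.5/6 = 25.0%.

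Cross-check: the last j places are all certain with probability 2·C(6−j,3)/C(6,3). For j = 1, 2, 3 this is 1.0 + 0.4 + 0.1 = 1.5. The sixth allocation is certain in every block.

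**Best guess.** The observer always guesses the arm with more places left and tosses a coin when they are equal. Expected correct guesses = 3 + (2⁶/20 − 1)/2 = 3 + (3.2 − 1)/2 = 4.1 of 6, or 68.3%. Full concealment gives 3 of 6, or 50%.

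**Scale.** Section 6b vi confirms ART eligibility after randomization, so the sequence runs over consented subjects: 0.25 × 600 = 150. At the same rate, 0.25 × 400 = 100 of those enrolled.

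**Varying block sizes.** Sequences of 600 were simulated with each block size drawn at random. The observer knows the set of possible sizes and all past allocations, but not the current size, and updates by Bayes' rule.

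| Block sizes | Certain | Best guess correct |
|---|---|---|
| 6 only (200 sequences, check) | 25.0% | 68.3% |
| 4 and 6 (100 sequences) | 5.5% | 69.4% |
| 4, 6 and 8 (100 sequences) | 2.4% | 68.0% |

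Varying the size cuts certainty about tenfold with 4, 6 and 8. It hardly changes best-guess accuracy.

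**The case against.** The strongest reply is that the assistant has little scope to act on a prediction. Patients are taken as they arrive, counselors make the first referral, and patients not referred and refusals both leave a record. Staggering is tied to equipment capacity, not to individual patients. The opinion-based exclusion is worded as the investigators' opinion. A patient who cannot stay that day is not lost to the rapid arm, since section 6c v keeps the rapid process open for 28 days. Nothing can be altered once the envelope is opened. If two assistants work without sharing results, neither sees the full sequence.

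Much of this stands, and it narrows the opportunity. It does not close it:

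- Consecutive recruitment is qualified by the staggering clause that follows it.
- Section 6b ii leaves the conclusion on the non-ART criteria to the assistant.
- Section 12d lists the assistant among those who inform patients, so counselor referral is not a complete barrier.
- Opening after consent prevents later manipulation, but not prediction beforehand.
- A log of refusals shows that a patient declined, not how the study was presented.

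It might also be said that concealment detail belongs in other study documents. Silence on envelope type or on who generates the list is indeed no fault. But section 6b iv itself states the block size, where the envelopes are kept and who opens them, and those stated choices are the point here.

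**Conclusion.** The design allows selection that one fixed block size makes needlessly easy. For an assistant who knows the block size and tracks the whole sequence, 25% of allocations are certain and 68% can be guessed. The share is lower with two assistants who do not pool results. The protocol does not say whether each clinic has its own sequence; if it does, the rate is the same at each.

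Three stronger readings are tempting and are not supported:

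- A reader might infer that a quarter of allocations will be known regardless. That depends on knowing the block size and the full sequence, and the protocol does not establish that any one assistant has both.
- A reader might infer that the primary comparison is biased. The documents show an opportunity, and give nothing from which to size a shift in the planned 50% v 70% comparison.
- A reader might infer that varying the blocks restores full concealment. It removes nearly all certainty, but a well-informed guess is still right about 68% of the time.

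The change is worth making because it is cheap and removes most of the certainty.

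**What to change.** Amend section 6b iv so that:

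- the list is generated off site by someone with no recruitment role, separately for each clinic;
- block sizes vary at random, for example among 4, 6 and 8;
- the block sizes are kept out of documents available to site staff;
- where existing staffing allows, someone other than the recruiting assistant opens the envelopes. This addresses the overlap of roles, which varying the blocks does not. It helps only so far as the recruiter does not then learn each result.

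The present rule of opening after consent and questionnaire should stay as it is.

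The cost is a new list and a short edit. Sample size, endpoint and clinical care are unchanged. Final arm sizes may differ by a few subjects per site: an unfinished block of 8 leaves a difference of at most 4 among those randomized, against 3 with blocks of 6.

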#### *6b v. Payment*

Following the blood draw, reimbursement to consented study subjects of R100 (approximately \$12.50) will be provided in the form of a voucher to a nearby supermarket or cell phone air time. An information card will be provided with the voucher, explaining where it can be used and noting that even though the voucher is identical to those sold as gift cards for all purposes, if it is used at the store

that is closest to the study clinic, the person redeeming it may be assumed to be participating in an HIV-related study.

#### *6b vi. Confirmation of treatment eligibility and study enrollment*

Under South African guidelines, ART eligibility is based primarily on CD4 count. Since a rapid CD4 count is part of the intervention for patients in the rapid group but not for those in the standard group, consent will take place before treatment eligibility is known. All subjects who meet other inclusion/exclusion criteria will be asked for consent, but only those who are treatment eligible will be enrolled in the study.

Procedures for performing a CD4 count are described below. Subjects in the rapid group will be informed as soon as their CD4 count result is available if they are eligible for treatment. Those who are not eligible on the basis of CD4 count and do not have symptoms of TB or a WHO Stage 4/3 condition will not be enrolled in the study. They will be given their CD4 count results following the clinic's standard procedures for returning laboratory results and asked to proceed with a standard pre-ART care or antenatal care visit.

Subjects in the rapid group who are eligible for treatment on the basis of CD4 count will be enrolled in the study and continue with study procedures as described below. Subjects in the rapid group who are not eligible for treatment on the basis of CD4 count but have symptoms of TB will be asked to remain in the clinic until initial TB test results are available (approximately 2 hours). Subjects who report symptoms that may indicate a Stage 4/3 condition will be examined to determine if a condition is present. Those diagnosed with TB or a Stage 4/3 condition will be enrolled in the study, while those without will be asked to proceed with a standard pre-ART care visit.

Subjects in the standard group of Track 1 will be advised to follow the standard schedule of clinic visits, which is to return to the site for their CD4 count results in 1 week. The study team will monitor CD4 count and TB test results and Stage 4/3 condition diagnoses and will enroll in the study only those who are eligible for treatment.

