## **1. Summary**

One of the most serious challenges facing antiretroviral therapy (ART) programs for HIV/AIDS in resource-constrained settings is the failure of ART-eligible patients to complete the steps required to initiate treatment. The high rate of loss to care of patients who are treatment-eligible at HIV diagnosis may be due in part to the large number of steps required between receiving an HIV diagnosis and obtaining the first dose of antiretrovirals (ARVs). In South Africa, these steps usually require approximately four clinic visits over a period of 2-8 weeks before a patient can start treatment. One strategy proposed for reducing losses among those eligible for ART is to simplify and condense the steps required for starting treatment. This is now possible because new, point-of-care (POC) tests for CD4 counts and TB diagnosis are available. These technologies can be combined with changes to clinic schedules to allow all steps required for ART initiation under South African guidelines (lab tests, physical exam, education) to take place on the day the patient presents for an HIV test.

This study is a randomized strategy evaluation of the feasibility, effectiveness, and cost-effectiveness of rapid ART initiation. Outpatient, non-pregnant, HIV-positive adults who come to a South African clinic for an HIV test, consent to study participation, and are eligible for ART will be randomized 1:1 to rapid ART initiation or to standard care. Those who are assigned to rapid ART initiation will have the possibility of receiving their first dose of ARVs as early as the same day, while those who are assigned to standard care will follow the clinic's usual procedures for starting ART. Rapid ART initiation for HIV-positive pregnant women, which has recently become the standard of care in South Africa, will also be assessed in a programmatic evaluation conducted alongside the randomized evaluation, with a retrospective comparison group. The primary study outcome for non-pregnant adults will be remaining alive, in care and virally suppressed 10 months after having a positive HIV test or CD4 count at the study site. The primary study outcome for pregnant women will be adherence to ART until delivery. The cost effectiveness of the rapid initiation strategy will be assessed as the cost per patient achieving the primary outcome for each population.

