##### *6c i. Rapid CD4 count and TB symptom screen*

The first step for rapid initiation will be a venous blood draw for a rapid CD4 count (and for other treatment initiation tests for those found eligible for treatment). For those offered rapid initiation, the blood sample will be processed immediately, on site, using the Pima Analyzer, rather than being stored for later transport to an off-site laboratory. The processing time for the Pima test is 20 minutes. In a validation study of Pima used at point of care clinics in South Africa, 7-9% of tests could not be read or had invalid results, due primarily to user errors in obtaining blood samples or filling cartridges. Careful training will be provided to study staff to minimize this type of error. A second Pima test will be run for subjects for whom the first Pima result is invalid. In addition, a blood sample will be sent to the off-site National Health Laboratory Service (NHLS) laboratory for all subjects in the rapid group for a confirmatory CD4 count. NHLS lab results will be monitored by the study team, and any subject found

not eligible for treatment using Pima but eligible based on lab results will be contacted by the study assistant and asked to return to the clinic to initiate treatment following rapid initiation procedures.

Patients who already have with them a valid CD4 count result (sample taken within the previous 6 months) will not have an additional CD4 count, though a blood sample will still be drawn for other required laboratory tests.

While awaiting CD4 test results, the study nurse will administer a TB symptom screen following South African guidelines for the definition of symptoms, for all subjects not already on TB treatment. Subjects with any TB symptoms will be asked to provide a sputum sample. The study nurse will also ask the subject about symptoms that might indicate a Stage 4/3 condition. Subjects who report such symptoms will be given a physical examination to determine if the condition exists and what treatment is needed.

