### *6c iii. Baseline lab tests, physical exam, and educational session*

Subjects who are eligible for ART will be enrolled in the study once treatment eligibility is confirmed. Using the same blood sample drawn earlier, the study nurse will perform the required baseline blood tests (creatinine, hemoglobin, ALT) and will perform a pregnancy test for female subjects in Track 1. (Track 1 rapid group subjects who are found to be pregnant will be transferred to Track 2 at this time.)

Subjects will then be examined by the study nurse, who will conduct the standard ART readiness physical examination. Either before or after the medical exam, depending on each day's patient flow, each subject will also meet individually or in a small group with the trained study assistant for an educational and counseling session on antiretroviral therapy, the importance of adherence and disclosure, and other actions to promote health while on ART. This will be a concise version of the education and counseling typically provided over the course of three visits under standard care. During this session, each subject will have an opportunity to ask questions and discuss concerns with the study assistant.

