#### *8f iv. Aggregate statistics*

Subjects who consent to study participation but are not eligible for ART and those who are found to be study ineligible for any other reason will not be enrolled in the study, as explained above. These subjects' ineligibility for the study will be confirmed by the lead data analyst. Data already collected for these subjects will be used to compile aggregate information on a monthly basis regarding patients at this site who are not eligible for treatment (e.g. average age and average CD4 count of patients who test HIV-positive). Individual data will be destroyed at the end of each month following compilation of the monthly aggregate statistics. Source documents for any test results (CD4 count, TB test result) generated during screening procedures will be retained in the study clinic's file for the patient.

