#### 11b. Clinical outcomes analysis

For both tracks and for primary and secondary clinical outcomes, the analytic approach for clinical outcomes will be the same. All analyses will be by intention-to-treat: subjects will be analyzed according to the intervention they were supposed to receive, whether or not they adhere to the defined intervention.

The analysis will begin with a simple comparison of the two treatment groups with respect to baseline predictors of outcomes. We will then conduct a crude analysis comparing the proportion of patients achieving each dichotomous outcome by group and crude risk ratios and 95% confidence intervals

stratified by group. For average gestational age at ART initiation and average time on ART before delivery for Track 2, we will calculate the mean difference between groups and corresponding 95% confidence interval.

Since adherence has been a particular concern for pregnant women who were not eligible for ART under the previous guidelines, the primary outcome for Track 2 will be stratified in secondary analysis by CD4 count at the time of initial ANC visit if enrollment numbers by the end of the study period are large enough to allow a stratified analysis. Subjects in the prospective group found after ART initiation to have CD4 counts above 350 will be compared to those in the retrospective group who were offered AZT under the previous guidelines, while subjects in the prospective group found after ART initiation to have CD4 counts below 350 will be compared to those in the retrospective group who were offered full ART under the previous guidelines.

Because we will not be randomizing large numbers of patients in Track 1 and because no randomization will occur in Track 2, it is possible that some baseline covariates may be imbalanced by treatment arm. To adjust for potential differences by baseline covariates, a log-linear regression model will be used to estimate adjusted risk ratios and a linear regression will be used to adjust mean differences.

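### Track 1 randomizes before ART eligibility is known and then selects the analysed subjects by means that differ between arms, so the intention-to-treat label does not protect the primary comparison

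*Protocol*

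**What the plan says.** The Protocol gives two accounts of who is randomized. Section 1 (Summary) says that patients who "consent to study participation, and are eligible for ART will be randomized 1:1 to rapid ART initiation or to standard care". Section 6b iv says otherwise: "After the questionnaire has been completed, subjects will be randomized to the rapid or standard groups of the study", and the arm-specific CD4 draw follows. Section 6b vi confirms that "consent will take place before treatment eligibility is known", because the rapid CD4 count is itself part of the intervention.

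After randomization, only subjects found eligible are enrolled. For the standard group, results and diagnoses are monitored and the team "will enroll in the study only those who are eligible for treatment". Section 10 plans 600 consented and 400 enrolled, so about 200 leave at this step.

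In the rapid arm, a subject found "not eligible for treatment using Pima but eligible based on lab results will be contacted by the study" assistant and brought back (section 6c i). Section 6c iii adds: "Track 1 rapid group subjects who are found to be pregnant will be transferred to Track 2 at this time".

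For those not enrolled, section 8f iv states: "Individual data will be destroyed at the end of each month following compilation of the monthly aggregate statistics". Section 11a i takes ART-eligible patients as the primary denominator and counts a missing six-month viral load as failure. Section 11b states: "All analyses will be by intention-to-treat: subjects will be analyzed according to the intervention they were supposed to receive".

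**The concern.** Dropping randomized subjects on a baseline value measured identically in both arms does no harm. Dropping them on information gathered differently by arm does, because the two groups left for analysis need not be comparable even though the randomized groups were. Some of the differential information, such as a TB diagnosis made at a later routine visit, also depends on staying in care, which bears on the outcome.

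Intention-to-treat as written in section 11b keeps enrolled subjects in their assigned arm. It does nothing for subjects removed between randomization and enrollment. At stake is the validity of the primary risk ratio. Because individual records of the non-enrolled are not kept, an all-randomized check at subject level would not be possible afterwards.

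**Working it through.** **1. The plan's own figure.** Inputs from section 10: 50% versus 70%, alpha 0.05 (two-sided reproduces), power 90%, uncorrected test.
n = [1.96·√(2·0.6·0.4) + 1.2816·√(0.25 + 0.21)]² / 0.20² = 124.0 per group. The stated 124 reproduces, and 124/0.70 = 177 to consent. The sample-size arithmetic is not at fault.

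**2. Routes to eligibility after randomization.**

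| Criterion | Rapid arm | Standard arm |
|---|---|---|
| CD4 ≤350 | Pima, repeated if invalid, plus a laboratory (NHLS) count that can add subjects; no rule removes a Pima-eligible, laboratory-ineligible subject (6c i) | One off-site laboratory count (6d i) |
| TB | Symptom screen by the study nurse, two Xpert tests if symptomatic (6c i, 6c ii) | Routine care at later visits (6d ii), found by monthly file review with no cut-off date (8f ii) |
| Stage 4/3 | Symptom enquiry and examination on the day (6b vi, 6c i) | Diagnoses recorded in routine care (6b vi) |
| Pregnancy found later | Transfer to Track 2 stated (6c iii) | Not stated |

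**3. Standard subjects with no sample or result.** Let f be the share of eligible standard subjects never ascertained and s their success rate. Both are assumptions; the Protocol gives neither.
Observed standard rate = (0.50 − f·s)/(1 − f).
- f = 5%, s = 0: 0.50/0.95 = 52.6%; the 20-point difference becomes 17.4.
- f = 10%, s = 0: 0.50/0.90 = 55.6%; it becomes 14.4.
- f = 5% or 10%, s = 25%: 51.3% or 52.8%.
- s = 50%: no shift at any f.
- f = 10%, s = 70%: 0.43/0.90 = 47.8%; the difference widens to 22.2.

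With no true effect (50% in both arms, about 200 per arm), the nominal 5% error becomes 8.1% or 19.1% for f = 5% or 10% with s = 0, and 5.8% or 8.4% with s = 25%.

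**4. Rapid subjects entering through TB alone.** Assume that the 30% not expected to be eligible (section 10) have CD4 >350, that 5-20% of them have TB (section 3b puts TB below 20%), and that the standard arm detects none.
- Upper end: 0.30 × 0.20 = 0.06, and 0.06/(0.70 + 0.06) = 7.9% of rapid enrollees.
- Lower end: 0.015/0.715 = 2.1%.

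At 7.9%, with success t among them, the rapid rate is 0.70·0.921 + 0.079·t: 64.5% at t = 0, 70% at t = 70%, 71.6% at t = 90%.

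**5. Either-test rule.** The Protocol gives no assay precision. A simulation with lognormal CD4, 70% at or below 350 and two independent readings with an assumed CV of 8-16% puts the rapid eligible share at about 72-74%, against 70% on one test.

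**6. Cost of analysing everyone randomized,** with non-eligible subjects counted as failures in both arms.
- 70% eligible: 0.70 × 0.50 = 35% versus 0.70 × 0.70 = 49%; 260 per group for 90% power; 93.7% power at 300 per group.
- 67% eligible: 33.5% versus 46.9%; 280 per group; 91.9% power at 300 per group.
- At 177 per group, power would be only 76.3% or 73.1%.

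**The case against.** The strongest reply is that most eligibility rests on CD4 and that the CD4 part is largely protected. Much of this stands.

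- A reader might infer that standard subjects who never come back drop out of the denominator, and so that the very pre-ART loss under study disappears. The documents do not support that. Laboratory results are monitored by the study team whether or not the patient returns (6b vi, 6d i), and such a subject counts as a failure (11a i). Only those with no sample or no result vanish. That group may be small: subjects are told their group after the draw and receive the voucher after it (6b iv, 6b v), although being sent to a different nurse may reveal the arm.
- Patients who return for a CD4 result are screened only if it is ≤350 (6b i), so their eligibility precedes randomization.
- Standard-arm TB and Stage 4/3 diagnoses also confer enrollment (6b vi), so the 7.9% is a ceiling.
- Pregnancy excludes from all of Track 1 (5c), and standard care also tests for it (6d ii). One-sided removal is what the text states, not proof of what would happen.
- A reader might also infer a large, irreparable bias in a known direction. The rates behind any figure are assumptions, and the calculation can shrink or widen the difference. Section 8f iv covers subjects confirmed ineligible; test source documents stay in clinic files, and allocation is reported monthly (8f iii). On the all-fail assumption, power at about 200 per arm would still be roughly 95% or 85%.

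Analysis sets are often left to an SAP. The order of randomization and sampling, and the destruction of records, are fixed here, and an SAP cannot repair them later.

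These points limit the CD4 component. They leave the either-test rule, the unequal TB and stage work-up, the pregnancy transfer and the open-ended file review.

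**Conclusion.** The point holds in this form. The Track 1 primary denominator is selected after randomization by means that differ between arms, the Summary misdescribes who is randomized, and the intention-to-treat statement covers only subjects who pass the selection. Four sources remain: the either-test CD4 rule, the more active TB and stage work-up in the rapid arm, the pregnancy transfer stated for that arm alone, and standard subjects with no sample or result.

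Neither size nor direction can be determined from the documents. The illustrative shift to 52.6-55.6% requires 5-10% non-ascertainment and failure in every such subject; it is zero if they do as well as the others. TB-only entrants are at most about 8% of rapid enrollees, and only if the standard arm detects none. The case for change is that the bias cannot be bounded afterwards and is cheap to prevent, not that it is shown to be large.

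**What to change.** 1. In 6b iv, draw the laboratory (NHLS) CD4 sample in both arms before the envelope is opened, or use the valid result the patient brings, under the same rule in both arms.
2. Define the Track 1 primary set as every randomized subject with CD4 ≤350 on that common baseline result, or with TB or a Stage 4/3 condition recorded before randomization. Report separately those eligible only through Pima, TB or stage findings made after randomization. Handle pregnancy and drug-resistant TB discovered later by one analysis rule applied identically to both arms.
3. Amend 8f iv to retain, de-identified, the arm, date, CD4 and reason for non-enrollment of every randomized subject. Add an all-randomized sensitivity analysis, which has about 92-94% power at 300 per group if 67-70% are eligible and non-eligible subjects count as failures.
4. Correct the Summary and the intention-to-treat wording in 11b to state who is randomized and who is analysed.

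The cost is a protocol amendment, a change in the order of one blood draw and a few retained fields. Both arms already have this test or a prior result, so no new test is needed. The downside is that a few percent of subjects, eligible only through findings after randomization, leave the primary set, and its population becomes slightly narrower.
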